### Assignment of Interventions

Participants will be prescreened from the OPD and inpatient department of consultant neurologists at NIMHANS by the designated study team. Following prescreening, the principal investigator (PI) will conduct formal screening procedures and enroll eligible participants. Allocation to study arms will be performed using a computer-generated randomization sequence prepared by an independent statistician from the funding agency (CCRAS). Allocation concealment will be ensured using the sequentially numbered, opaque, sealed envelopes approach to prevent selection bias during participant enrollment. Once the patient is enrolled, the study PI shall provide the sequentially numbered envelope with the group allocation concealed inside to the participant who will open it.

The Ayurvedic interventions will be administered by the PI, who is a qualified Ayurveda physician. Standard conventional care will continue to be managed by the participant’s treating neurologist, as per routine clinical practice. However, the assessor conducting the assessments will remain blinded to group allocation to minimize bias.

### Intervention

The interventions used in this study consist of two arms: group A (control group) receiving conventional TAU and group B (intervention group) receiving add-on Ayurveda therapy along with TAU of PD, prescribed by the treating neurologist.

#### Group A (Conventional TAU—Control Group)

Participants will receive pharmacological treatment as prescribed by the treating neurologist. This would include tablet levodopa and carbidopa 125 mg or tablet entacapone 200 mg or tablet pramipexol 1 mg or tablet selegiline 5 mg as appropriate per the assessment of the consultant neurologist.

#### Group B (Conventional TAU With Add-On Ayurveda—Intervention Group)

Participants will receive Ayurveda intervention as an adjunct to the conventional treatment for a period of 180 days, comprising 3 cycles of Ayurveda therapies at 60-day intervals. The regimen is structured as follows:

Preparatory phase (*Deepana-Pachana* therapy): To enhance digestion and metabolism, participants will be administered *Chitrakadi Vati* (250 mg per tablet), 2 tablets with warm water, 3 times daily before food for a duration of 5 days.Shodhana therapy (purification phase—*Basti* [rectal administration of medicine] therapy): This includes a Yoga Basti regimen, wherein a combination of *Niruha Basti* (therapeutic decoction enema) and *Anuvasana Basti* (oil enema) will be administered in a prespecified regimen in the form of *Basti* comprising one *Sneha Basti* initially, 3 decoction *Bastis* alternately followed by 3 *Sneha Bastis,* and 1 *Sneha Basti* in the end aimed at pacifying *Vāta Dosha*.Niruha Basti: Decoction of *Erandamoola* (made with the root of *Ricinus Communis* Linn [450 mL]) administered rectally on an empty stomach as per the protocol for *Yoga Basti*.*Anuvasana Basti*: *Bala Taila* (90 mL) administered immediately after food on 5 occasions as per the protocol for *Yoga Basti*.Shamana therapy (pacificatory phase): Following purification, the participants will receive oral Ayurveda formulations for symptomatic relief and alleviation of vitiated *Vata Dosha* for 47 days in each cycle as follows:*Mashabaladi Kwatha* (decoction)—15 mL, with 2 pinches of asafoetida and rock salt administered with warm water 3 times daily.*Kalyanaka Ghrita* (medicated ghee)—20 mL, taken early in the morning on an empty stomach.The complete Ayurveda intervention regimen will be repeated thrice over the study period, with 3 cycles of 60 days each, totaling 180 days.

Usual concomitant care (if any), including physiotherapy and occupational therapy, will be permitted as part of standard management and will be recorded as concomitant therapy. However, the use of any additional Ayurvedic therapies or herbs not specified in the study protocol will be prohibited during the trial to avoid confounding effects. All concomitant medications, including any dose modifications of standard medications or rescue interventions required for symptom management, will be documented at each study visit in the case report forms.

### Strategies for Improving the Fidelity of Care Providers and Adherence of Participants

The Ayurvedic intervention is standardized and will be administered uniformly as per the protocol. Participants will be screened for suitability before Panchakarma therapy, and the intervention will be withheld in cases of intolerance, fever, respiratory infection, or any other clinical contraindication. To ensure uniformity, all procedures will follow standard operating protocols, and participants will receive patient information leaflets detailing the interventions.

As panchakarma therapies are delivered in an inpatient or closely supervised setting by trained professionals, adherence will be monitored daily through direct supervision and treatment logs. Participants are required to maintain a compliance form to record the intake of both standard care and add-on oral Ayurvedic medications, which will be reviewed by the study team during follow-up visits. Furthermore, to promote participant retention and minimize missing data, follow-up will be reinforced through periodic telephonic contact between scheduled visits.

### Outcome Measures

The primary outcome is the change in the total score of the Movement Disorder Society-UPDRS (MDS-UPDRS) after 6 months of treatment, compared with the baseline. MDS-UPDRS Part III will be assessed in both the ON and OFF medication states. The OFF state assessment will be conducted after a 12-hour withdrawal from the patient’s last dopaminergic medication, whereas the ON state assessment will be performed 1 hour after the administration of the first morning dose of dopaminergic medication. The OFF-state evaluation (after 12 h withdrawal) reflects the underlying disease severity, whereas the ON-state evaluation (1-h postmorning dose) reflects treatment responsiveness. The total MDS-UPDRS change is thus intended to integrate both clinical states, which is relevant for this exploratory phase of the Ayurvedic add-on intervention assessment.

The secondary outcome measures include a range of neurophysiological, biochemical, cognitive, and functional parameters. Cortical excitability will be assessed using TMS, evaluating both single-pulse (MT, resting cortical, and SP) and paired-pulse (SICI, LICI, and ICF) measures. Autonomic function will be analyzed through HRV, whereas pulmonary function tests will assess respiratory capacity.

Exploratory mechanistic outcomes include alterations in immunological markers, including changes in Th1/Th2/Th17/T regulatory cell populations, plasma levels of pro-inflammatory cytokines, and telomere length, which will be measured to evaluate the immunomodulatory and anti-inflammatory effects of the intervention.

Functional and motor outcomes will be examined through reductions in dyskinesia severity using the Unified Dyskinesia Rating Scale and improvements in gait parameters, measured using the 6-minute walk test and gait speed (10-m walk test). Cognitive function will be assessed using the Montreal Cognitive Assessment, and postural stability will be evaluated through the Balance Error Scoring System. Changes in Scales for Outcomes in Parkinson’s disease-Sleep will be monitored to assess improvements in sleep disturbances associated with PD.

Safety assessments will include monitoring for treatment-emergent adverse events throughout the study period. Liver function tests, renal function tests, and complete blood count will be performed at baseline and at the end of the study (day 180) to detect any potential systemic adverse effects. For participants undergoing Basti therapy, adverse events (AEs) will be monitored during the in-patient care.

Participants in the TAU arm will continue with their dopaminergic medications. At baseline, stabilized or optimized dopaminergic doses will be recorded, and any subsequent changes during the trial will be documented along with dates and reasons. Levodopa equivalent daily dose (LEDD) will be calculated at each visit (baseline and follow-ups) using standardized conversion factors and tracked longitudinally.

All clinical and neurophysiological outcome assessments will be performed by a trained SRF with an MD (Ayurveda) qualification, and the routine assessments will be done by the neurologists involved in the study before prescribing the study TAU interventions or deciding changes in interventions. The SRF underwent a 3-month structured training program under the supervision of a neurologist and neurophysiologist to ensure competency in administering both clinical and neurophysiological assessments. The same SRF will also be responsible for data collection throughout the study to maintain consistency.

All outcome measures are evaluated using validated clinical scales and standardized laboratory instruments, as detailed in the manuscript, each with established reliability and validity. Before the commencement of data collection, all laboratory instruments and procedures will be calibrated and standardized. To promote data quality, assessors received formal training, and interrater reliability for the primary outcome measure (MDS-UPDRS Part III) will be established in at least 20% of participants.

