**Figure 1. F1:**
[figure not shown]
Study design. TAU: treatment as usual.

Participants will be followed for 24 weeks post-randomization. The study aims to generate preliminary evidence on clinical efficacy and mechanistic insights related to cortical excitability, neuroimmune function, and autonomic function. Participants will be randomized into either the add-on Ayurveda intervention arm or the TAU control arm, with each participant undergoing a 6-month study period.

Participants will be recruited from both the outpatient department (OPD) and inpatient department services of the Departments of Neurology and Integrative Medicine at the NIMHANS, Bengaluru, India. NIMHANS is a tertiary care neuropsychiatric and neurosciences hospital and Institute of National Importance under the Ministry of Health and Family Welfare, Government of India. The study will be conducted within NIMHANS using its specialized neurology and integrative medicine infrastructure for recruitment, intervention delivery, and follow-up assessments.

Those meeting the inclusion criteria will be recruited after obtaining written informed consent. Informed consent will be obtained by the senior research fellow (SRF) possessing an MD (Ayurveda) qualification, who has been trained in Good Clinical Practice (GCP) [14] and institutional ethical guidelines for human research. The study procedures, potential benefits, risks, and the right to withdraw at any stage will be clearly explained in the patient’s language, and a copy of the consent document will be provided (Multimedia Appendix 1).

To promote adequate enrollment, participants will be recruited through advertisements in print and institutional media, as well as by prescreening of hospital health records to identify potentially eligible individuals. Efforts will also be made to minimize participant burden by providing clear information, convenient scheduling of assessments, and coordinated support from study staff during recruitment and follow-up.

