### Brief Description of Some Relevant Assessments

#### Clinical Assessments

##### Movement Disorder Society–Unified Parkinson’s Disease Rating Scale

This scale assesses motor and nonmotor PD symptoms. It includes four parts: nonmotor experiences of daily living (part I), motor experiences of daily living (part II), motor examination (part III), and motor complications (part IV). Parts IA, IB, and II are conducted in the “ON” state, whereas Part III is assessed in both “ON” and “OFF” states. Part IV integrates patient-reported information with clinical observations [18].

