### Statistical Analysis

All analyses will be performed using SPSS software. The primary outcome, change in MDS-UPDRS Part III score from baseline to 24 weeks, will be analyzed using a mixed model for repeated measures with treatment, time, and treatment×time interaction as fixed effects and baseline values as covariates. LEDD will be included as a time-varying covariate to account for dopaminergic medication effects. Results will be reported as least-square mean differences with 95% CIs. The main analysis will follow a modified intention-to-treat approach including all randomized participants who receive at least one dose of the assigned intervention, whereas a per-protocol analysis will be performed as a sensitivity check on participants who complete ≥80% of scheduled therapies and medication adherence.

Missing data will be handled under the assumption of data missing at random using the mixed model for repeated measures model, which uses all available data without imputation. Additional sensitivity analyses, including multiple imputation and complete case analyses, will be performed to evaluate the robustness of results. The secondary outcomes will be analyzed using appropriate mixed or generalized linear models and interpreted as exploratory. Descriptive statistics will summarize categorical variables as frequencies and percentages, and continuous variables as mean (SD), median (IQR), and range.

Predefined subgroup analyses will explore whether treatment effects differ by baseline Hoehn and Yahr stage (≤3.0 vs >3.0), disease duration (<5 vs ≥5 y), age (<65 vs ≥65 y), baseline LEDD (≤ median vs >median), and presence of dyskinesia. Interaction terms will be tested using mixed effects models, and the results will be interpreted as exploratory. Sensitivity analyses will include assessing participants with stable dopaminergic doses (<10% LEDD change) and testing the interaction between treatment allocation and LEDD change to explore medication-dependent effects. Safety analyses will be descriptive, summarizing AEs and serious AEs by treatment group.

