### Harms: AE Collection, Assessment, Reporting, and Management

Participants will be assessed for AEs at each scheduled follow-up visit (days 60, 120, and 180) and during routine hospital visits. Each reported AE will be documented and categorized based on severity, relatedness to the intervention, and expectedness, following standardized guidelines. Laboratory safety assessments, including liver function tests, RFTs, and complete blood count, will be performed at baseline and at the final study visit (day 180) to monitor any potential systemic effects. All recorded AEs will be reviewed by the DSMB, which will assess their clinical significance and provide recommendations for participant safety. SAEs will be promptly reported to the NIMHANS Human Ethics Committee and the sponsor, CCRAS, in accordance with regulatory guidelines.

For participants who discontinue or deviate from the intervention protocol, no further outcome assessments will be conducted, as the primary outcome (MDS-UPDRS Part III) requires evaluation in both ON and OFF medication states, and other assessments (TMS, pulmonary function tests, Montreal Cognitive Assessment, 6-m walk test, and Balance Error Scoring System) are performed in the OFF state. The reasons for nonadherence (eg, adverse effects, lack of perceived benefit, or personal constraints) and nonretention (eg, withdrawal or loss to follow-up) will be systematically documented either during the next scheduled visit or through telephonic communication. These details will be recorded in the case report forms to enable transparent reporting and analysis of participant flow and data completeness.

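### The primary outcome is the MDS-UPDRS total score in one place and Part III in three others, with no medication state or combining rule, so the protocol does not identify its primary result.

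*Protocol article*

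**What the plan says.** The protocol article names the primary outcome four times.

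- Outcome Measures, opening sentence: "The primary outcome is the change in the total score of the Movement Disorder Society-UPDRS (MDS-UPDRS) after 6 months of treatment".
- Outcome Measures, closing sentence on assessor training: "interrater reliability for the primary outcome measure (MDS-UPDRS Part III) will be established in at least 20% of participants".
- Statistical Analysis: "The primary outcome, change in MDS-UPDRS Part III score from baseline to 24 weeks, will be analyzed using a mixed model for repeated measures".
- Harms, on participants who discontinue: "the primary outcome (MDS-UPDRS Part III) requires evaluation in both ON and OFF medication states".

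On medication state, Outcome Measures says "MDS-UPDRS Part III will be assessed in both the ON and OFF medication states", and the description of the scale says "Parts IA, IB, and II are conducted in the “ON” state, whereas Part III is assessed in both “ON” and “OFF” states". On how the two Part III scores reach the total, there is one sentence: "The total MDS-UPDRS change is thus intended to integrate both clinical states". Statistical Analysis gives no state for the Part III score it models.

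**The concern.** The scale has four parts and Part III is one of them, so change in the total and change in Part III are different endpoints. The model under Statistical Analysis does not analyse the endpoint that opens Outcome Measures.

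The state is a second open choice. By the protocol's own account the two states measure different things: OFF reflects underlying severity and ON reflects response to treatment. An add-on therapy could move one and not the other.

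The separation between one primary outcome and a set of secondary outcomes read as exploratory works only if the primary is fixed. As written, several analyses could each be presented as the planned primary result, and a reader of the final report could not tell whether the choice was made before or after the data were seen.

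**Working it through.** **Step 1. Set the statements side by side.**

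| Place | Score named as primary | State | Rule for ON and OFF |
|---|---|---|---|
| Outcome Measures, opening | Total | both intended | none |
| Outcome Measures, assessor training | Part III | not given | none |
| Statistical Analysis (primary model) | Part III | not given | none |
| Harms, discontinuation | Part III | both required | none |

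The contradiction lies inside Outcome Measures as well as between it and two other sections. It is not a single slip: Outcome Measures gives a reason for using the total, and Harms uses Part III as its reason for ending assessments after discontinuation.

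**Step 2. Look for a passage that settles it.** Sample Size refers only to a UPDRS score (mean change 1.0, SD 2.0, correlation 0.60) and names neither part nor state. Table 2 lists the MDS-UPDRS as one row. Neither resolves the question.

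**Step 3. Count the candidates.** The count depends on how the text is read.

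- Two: total against Part III, each in some one form.
- Three: Part III ON, Part III OFF, and one total integrating both states.
- Four: Part III ON, Part III OFF, total with ON, total with OFF.
- Five: those four plus a total using both Part III scores.

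**Step 4. Illustrate the effect of an open choice.** The protocol gives no figure to reproduce here. Assume k test statistics, standard normal under no effect, with a common pairwise correlation r that the documents do not give:

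Z_i = √r·U + √(1−r)·E_i, with U and the E_i independent standard normal.

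P(at least one |Z_i| > 1.96) = 1 − ∫ φ(u)·[Φ((1.96 − √r·u)/√(1−r)) − Φ((−1.96 − √r·u)/√(1−r))]^k du

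| k | r = 0.7 | r = 0.8 | r = 0.9 |
|---|---|---|---|
| 2 | 8.3% | 7.8% | 7.0% |
| 3 | 10.9% | 9.8% | 8.4% |
| 4 | 13.0% | 11.4% | 9.4% |
| 5 | 14.8% | 12.7% | 10.2% |

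Numerical integration gives these values, and a simulation of 400,000 draws for k = 3 to 5 at r = 0.7 and 0.9 agrees to about 0.1 percentage point. The range is about 7% to 15%, against a nominal 5%.

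**Step 5. Check the time point.** Outcome Measures says 6 months and Statistical Analysis says 24 weeks; Trial Design says "Participants will be followed for 24 weeks post-randomization". Table 2 has visits at baseline and days 60, 120 and 180 only. Twenty-four weeks is 24 × 7 = 168 days, and no visit falls there. All three labels can only mean the day-180 visit.

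**The case against.** The best defence is that the trial calls itself exploratory, the data analyst is blinded to allocation, no interim analysis is planned, and an unseen analysis plan may name one endpoint. These points lower the risk of a choice driven by the data. They do not remove the contradiction. An analysis plan can add detail to a defined endpoint, but here the article states two. The trial is also described as a superiority trial, sized with a two-tailed alpha of 0.05 and 80% power, so its primary result will be read as a test.

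Several stronger readings are tempting, and the documents do not support them.

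- *The time point is a further free choice.* It is not, because there is only one final visit. The 24-week label is a wording fault.
- *The total must either count Part III twice or silently pick one state.* Averaging ON and OFF is a third possibility, and picking one state would conflict with the stated intention to integrate both. What is missing is the rule. For the same reason, the candidates built as a total with one state fit the text less well, and a reader who drops them is left with three candidates (about 8% to 11%).
- *The total is open to bias from unblinded participants while Part III is protected.* Patient-reported information is stated only for Part IV, and one assessor, blinded to allocation, performs all clinical outcome assessments. The documents do not establish the contrast.
- *OFF is the natural state to choose.* Outcome Measures gives a reason for each state, and the Hypothesis section expects a better response to levodopa, which speaks at least as well for ON.

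**Conclusion.** The point stands in this form: the protocol states two different primary outcomes, the primary model analyses only one of them, and nothing fixes the medication state or the rule for combining the two Part III scores. This rests on wording alone and needs no assumption.

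The 7% to 15% range is an illustration. It assumes two to five candidates, equal correlations of 0.7 to 0.9, and a report that picks any candidate reaching significance. A reader might take it as the trial's actual error rate. It is not a property of the plan, since the documents give no correlations and no sign that such picking is intended.

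The point should be settled before analysis. At the August 2025 count, 33 of 58 enrolled participants had completed, and completion is scheduled for September 2026.

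**What to change.** Before any unblinded look at outcome data, amend both statements in Outcome Measures, the one in Statistical Analysis and the one in Harms so that they name the same endpoint:

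1. One score. Part III causes the least disruption, because three of the four statements and the primary model already use it.
2. One named medication state, or one explicit rule combining ON and OFF. The investigators should choose and give the reason.
3. One time point, the day-180 visit.

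List the remaining versions as secondary. If a total is kept among them, state how Part III enters it. As a wording repair, replace 24 weeks by day 180 under Trial Design and Statistical Analysis.

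The cost is a protocol amendment and a matching registry entry. Table 2 already schedules the MDS-UPDRS at every visit. It does not say that Part III is done in both states at each of them, so the amendment should confirm that the chosen score is collected at every visit the model uses.

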##### Unified Dyskinesia Rating Scale

This tool evaluates involuntary movements (dyskinesia) associated with PD treatment. It includes historical (on-dyskinesia and off-dystonia) and objective (impairment and disability) sections, focusing on choreic and dystonic movements [19].

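### If the total MDS-UPDRS is primary, as Outcome Measures states, it includes participant-reported parts that assessor blinding cannot protect; naming Part III, as Statistical Analysis does, largely removes the problem

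*Protocol article*

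**What the plan says.** All references are to the protocol article.

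**The primary outcome has two definitions.**
- Outcome Measures: "The primary outcome is the change in the total score of the Movement Disorder Society-UPDRS (MDS-UPDRS) after 6 months of treatment". The section justifies the total as a way to bring the ON and OFF states together.
- Later in the same section, on data quality: "interrater reliability for the primary outcome measure (MDS-UPDRS Part III) will be established in at least 20% of participants".
- Statistical Analysis: "The primary outcome, change in MDS-UPDRS Part III score from baseline to 24 weeks". The mixed model is specified for this score.
- Harms: "the primary outcome (MDS-UPDRS Part III) requires evaluation in both ON and OFF medication states".

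**What the total contains.** The scale's description lists four parts. Parts I and II cover nonmotor and motor experiences of daily living, Part III is the motor examination, and for the last it says: "Part IV integrates patient-reported information with clinical observations".

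**Who knows the allocation.** Under Assignment of Interventions, the principal investigator is to "provide the sequentially numbered envelope with the group allocation concealed inside to the participant who will open it". The Intervention section sets add-on Ayurveda with usual treatment against usual treatment alone and describes no sham. The stated safeguard for measurement is that "the assessor conducting the assessments will remain blinded to group allocation to minimize bias".

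**Related scales.** The sleep scale asks about problems over the past month. Of the dyskinesia scale the article says: "It includes historical (on-dyskinesia and off-dystonia) and objective (impairment and disability) sections".

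**The concern.** Blinding the assessor protects what the assessor observes and scores. It does not protect an answer whose source is a participant who knows the arm. In this trial only the add-on arm receives repeated enema therapy in an inpatient or closely supervised setting, so expectation and staff contact may differ between arms. Either could move self-reported scores without any change in the disease.

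If such answers are added to the examination score, the primary contrast mixes a blinded component with an open one. A between-arm difference in that total could not be read, on its own, as blinded evidence. This matters because the trial is described as an assessor-blinded superiority trial, and the Discussion expects its findings to bear on guidelines and policy. The article does not acknowledge the limitation.

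The point is distinct from whether the assessor stays blind. It holds even if that blinding is perfect. It does depend on which definition of the primary outcome applies.

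**Working it through.** The plan states no figure on this point, so the check is mainly a comparison of sections, followed by two calculations on stated assumptions.

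**Step 1. Which safeguard covers which bias.**
- Computer-generated sequence from an independent statistician (Assignment of Interventions): selection.
- Sequentially numbered, opaque, sealed envelopes (same section): selection.
- Blinded data analyst (data handling section): analysis.
- Blinded assessor (Assignment of Interventions): outcome measurement.

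Only the last acts on measurement, and only on what the assessor rates.

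**Step 2. Which parts it reaches.**
- Part III is a motor examination, so assessor blinding applies.
- Part IV is described as partly patient-reported, so it applies in part.
- Parts I and II are not expressly called patient-reported. Experiences of daily living cannot be obtained by a motor examination, so participant report is a reasonable inference, but it is an inference.

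**Step 3. Share of the total affected.** The documents give neither item counts nor part maxima. Assume maxima of 52, 52, 132 and 24 for Parts I to IV. The documents also do not say how ON and OFF enter the total, so both ways of counting Part III are shown.

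| Definition | Maximum | Parts I + II | Parts I + II + all of IV |
|---|---|---|---|
| Part III counted once | 52 + 52 + 132 + 24 = 260 | 104/260 = 40% | 128/260 = 49% |
| Part III counted ON and OFF | 260 + 132 = 392 | 104/392 = 27% | 128/392 = 33% |
| Part III alone is primary | not applicable | 0% | 0% |

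**Step 4. Illustration of the consequence.** Assume no true effect, a reporting shift of d standard deviations of the analysed score in one arm, and a two-sided 5% test. The normal approximation is

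P(significant) = Φ(d/se − 1.96) + Φ(−d/se − 1.96), with se = √(2/n) in SD units.

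For n = 28 per arm (the Sample Size figure), se = √(2/28) = 0.267.
- d = 0.2: d/se = 0.748, so Φ(−1.212) + Φ(−2.708) = 0.116. The noncentral t gives 0.114.
- d = 0.3: d/se = 1.122, so Φ(−0.838) + Φ(−3.082) = 0.202. The noncentral t gives 0.197.

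The rate therefore rises from 5% to about 11% or 20%. With 40 per arm, the recruitment target, the normal approximation gives 0.145 and 0.269. A larger sample does not cure the problem, because it makes a biased difference easier to detect.

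The size of d is assumed; nothing in the documents estimates it. The planned analysis is a baseline-adjusted mixed model, not a t test, so these rates show direction and order of magnitude only.

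**The case against.** The strongest reply is that the operative analysis already avoids the problem. Statistical Analysis fits its model to Part III and gives no primary model for the total. The reliability plan and the Harms section also name Part III. If Outcome Measures is brought into line with them, little remains for the primary outcome. This stands, and it makes the point conditional. It does not dispose of it: the sentence that defines the primary outcome names the total and gives a reason for it, so the sections could equally be reconciled towards the total, which would keep the open components in.

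The trial also calls itself exploratory, and secondary outcomes are to be interpreted as exploratory. That softens the matter for the sleep and dyskinesia scales, which are already separate from the primary outcome. It does not cover how a primary total would be described.

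Three stronger readings are tempting, and the documents do not support them.
- A reader might infer that assessor blinding is the trial's only protection against bias. It is not: randomisation, allocation concealment and a blinded analyst are all stated.
- A reader might take it as fact that a large share of the primary score is self-reported. Only Part IV is expressly so described, and the share runs from 0% to 49% depending on the definition and on assumed maxima.
- A reader might set a one-point reporting shift against the Sample Size inputs and obtain a false-positive rate of 45% (SD 2.0) or 54% (SD of change 2.0 × √(2 × (1 − 0.60)) = 1.79) with 28 per arm. The arithmetic is right, but the shift is chosen, and the SD comes from a prior study's UPDRS score that is not shown to apply to the MDS-UPDRS total. With a larger SD, a one-point shift would matter less.

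**Conclusion.** The concern holds conditionally. Under the definition in Outcome Measures, the primary score includes components that come wholly or partly from participants who know their allocation, and the one stated safeguard on measurement does not protect them. Under the definition in Statistical Analysis, the concern largely falls away for the primary outcome. It remains for Parts I, II and IV, the sleep scale and the historical section of the dyskinesia scale as secondary outcomes.

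The conclusion rests on two things beyond the text: the inference that Parts I and II are participant-reported, and the assumed part maxima behind the 27% to 49% range. The error rates of about 11% and 20% are illustrations, not estimates of bias in this trial. The documents do not show that such bias has occurred, nor do they say that a total-score result would be reported as blinded evidence. This is a worthwhile improvement to make before the data are analysed by arm.

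**What to change.** 1. In Outcome Measures, replace the total score with MDS-UPDRS Part III scored by the blinded assessor, so that the definition agrees with Statistical Analysis, the reliability plan and Harms.
2. Report Parts I, II and IV, any total score, the sleep scale and the historical section of the dyskinesia scale separately as secondary outcomes, labelled as participant-reported (for Part IV, partly so) under open allocation. Show the objective section of the dyskinesia scale on its own.
3. State in advance that a benefit seen only in those participant-reported measures or in the total, without a Part III benefit, will not be presented as assessor-blinded evidence of efficacy.

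**Cost.** No new data are needed: the whole scale is already scheduled at every visit and its parts can be scored separately. The downside is that participant-reported burden moves from the primary outcome to the secondary ones. By August 2025, 58 participants were enrolled and 33 had completed, so the change should be dated and documented. If it counts as substantial under Protocol Amendments, it needs ethics committee approval. No interim analysis is planned, so it can still be made before any comparison of the arms.
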